## Abstract

**Background:**

Previous evidence supports the efficacy and safety of intravenous urokinase thrombolysis in acute ischemic stroke (AIS), with additional advantages in terms of cost-effectiveness. Existing studies suggest that treatment response may be dose-dependent; however, current dosing practices remain largely empirical and lack standardization based on high-quality evidence. Establishing a weight-based dosing regimen is, therefore, essential to maximize therapeutic benefit and minimize risks.

**Objective:**

To determine the maximum tolerated dose (MTD) of urokinase and to develop an optimized weight-adjusted dosing protocol for AIS.

**Methods:**

OUTSET is a prospective, single-center, phase I, dose-escalation clinical trial using a weight-based, rolling-six design in patients with AIS. Patients who meet the inclusion criteria will be assigned to one of four dose groups (15,000 IU/kg, 20,000 IU/kg, 25,000 IU/kg and 30,000 IU/kg). Urokinase will be administered intravenously, diluted in 100 mL of normal saline, over a period of 30 min.

**Outcomes:**

The primary endpoint is the identification of the MTD based on dose-limiting toxicity events, including symptomatic intracranial hemorrhage, major bleeding, and other significant adverse events.

**Discussion:**

This study offers a structured, weight-based approach to determining the MTD of intravenous urokinase for AIS using a rolling-six dose-escalation design. By addressing the current lack of standardized, body-weight–adjusted dosing protocols, the findings may enhance the clinical safety and efficacy of urokinase thrombolysis. The results are expected to inform future phase II/III trials and support the development of individualized thrombolytic strategies in routine stroke care.

**Clinical trial registration:**

ClinicalTrials.gov identifier: NCT07047326.

## Introduction

Acute ischemic stroke (AIS) remains a leading cause of death and long-term disability worldwide. Intravenous thrombolysis (IVT) is among the most effective strategies for restoring cerebral perfusion and improving functional outcomes in AIS. However, the accessibility and utilization of IVT vary substantially across regions. While approximately 10–15% of patients in high-income countries receive IVT, this proportion falls below 2% in many low- and middle-income regions (1). Such disparities are influenced by multiple factors, including geographical and logistical barriers, yet economic affordability remains one of the most critical constraints (2). The high cost of recombinant tissue plasminogen activators such as alteplase and tenecteplase poses a major barrier to the widespread implementation of IVT, particularly in resource-limited settings (3–5).

Urokinase, a human-derived serine protease that directly converts plasminogen to plasmin, represents a cost-effective alternative thrombolytic agent (6). Decades of clinical experience and several clinical studies have demonstrated its efficacy in promoting recanalization and improving neurological outcomes in AIS. The Chinese Guidelines for the Diagnosis and Treatment of Ischemic Stroke recommend intravenous administration of 1.0–1.5 million international units (IU) of urokinase within 6 h of symptom onset (7, 8). In contemporary IVT practice, however, urokinase addresses a different research question from alteplase and tenecteplase. For alteplase, the weight-based regimen has already been well established (9, 10), whereas recent studies of tenecteplase have mainly focused on whether it may serve as a safe and effective alternative to alteplase in eligible patients with AIS (10–12). By contrast, for urokinase, the more immediate question is not simply whether it can replace another thrombolytic agent, but how its dosage should be optimized scientifically in current clinical practice. This issue is clinically important because urokinase remains relevant in China and other resource-limited settings owing to its affordability and accessibility, while available comparative evidence suggests that its effectiveness and safety may be broadly comparable to those of alteplase (6, 13, 14). Recent observational data further suggest that higher weight-adjusted doses (23,400–30,000 IU/kg) of urokinase may be associated with improved functional outcomes compared with lower-dose groups, without a corresponding increase in symptomatic intracranial hemorrhage (15). However, a weight-adjusted dosing regimen for urokinase thrombolysis remains unknown.

To address this critical knowledge gap, we designed the Dose-Escalation Safety Study of Urokinase for Thrombolysis in Patients with Acute Ischemic Stroke (OUTSET), a single-center, phase I clinical trial employing a rolling-six dose-escalation design. This study aims to determine the maximum tolerated dose (MTD) and to evaluate the safety and tolerability of weight-based urokinase thrombolysis, thereby establishing an evidence-based foundation for subsequent multicenter efficacy trials.

## Methods and analysis

This study is a prospective, single-center, open-label, phase I, single-arm, dose-escalation clinical trial. A rolling-six design (16–19), a rule-based phase I dose-escalation method that allows concurrent enrollment of 2 to 6 participants at a given dose level, will be used (16). This design was selected because it reduces delays associated with sequential enrollment and can provide more safety information than the conventional 3 + 3 approach (16, 20). The study design is illustrated in Figure 1. The primary objective is to determine the MTD of urokinase thrombolysis in patients with AIS and to develop an optimal weight-based dosing regimen. This study has been approved by the Ethics Committee of Xuanwu Hospital and registered with Clinicaltrials.gov (Identifier: NCT07047326). All participants will provide written informed consent prior to enrollment in the study.

**Figure 1 fig1:**
[figure not shown]
Rolling-six dose-escalation design for determining the MTD of intravenous urokinase in AIS. The figure shows the decision process based on the number of enrolled and evaluable patients, the occurrence of DLTs, and the number of patients still at risk for DLTs. Depending on these factors, dose escalation, cohort expansion, or termination decisions are made. The MTD is defined by the number of DLTs observed at each dose level. DLT, dose-limiting toxicity; MTD, maximum tolerated dose; AIS, acute ischemic stroke.

### Participants

Patients will be eligible for enrollment if they present with AIS. The inclusion criteria include:

Age 18–80 years.AIS that can be treated within 6 h of symptom onset (the time of symptom onset is defined as “the last time point at which the patient appears normal”).The National Institutes of Health Stroke Scale (NIHSS) ≥1, with symptoms considered clinically disabling or otherwise judged by the treating investigator to warrant intravenous thrombolysis.Subjects or their guardians voluntarily sign the informed consent.

Exclusion criteria are as follows:

Head CT or MRI shows a large infarction (infarcted area >1/3 of the middle cerebral artery).Unknown time of stroke onset.Pre-stroke modified Rankin Scale (mRS) score ≥2.NIHSS score 1A ≥2.Intracranial hemorrhage (including parenchymal hemorrhage, intraventricular hemorrhage, subarachnoid hemorrhage, subdural/extradural hematoma, etc.).A history of intracranial hemorrhage.Propensity for acute bleeding, including platelet count <100 × 10^9^/L or otherwise.Having received heparin treatment within 24 h.On oral anticoagulants (e.g., warfarin) with INR >1.7 or PT >15 s;Patients with planned or prior endovascular therapy.A history of severe head trauma or stroke within 3 months.Intracranial tumors, large intracranial aneurysms.A history of intracranial or spinal surgery within 3 months.A history of major surgery within 2 weeks.Severe liver impairment (e.g., liver failure, cirrhosis, portal hypertension [esophageal varices], active hepatitis).A history of gastrointestinal or urinary tract hemorrhage within 3 weeks.Active visceral bleeding.Aortic dissection found.A history of arterial puncture at sites difficult for compression hemostasis within 1 week.Life expectancy <1 year due to comorbid conditions.Uncontrollable hypertension upon active antihypertensive treatment: systolic blood pressure ≥180 mm Hg, or diastolic blood pressure ≥100 mm Hg on ≥3 repeated measurements at 10-min intervals.Blood glucose <2.8 mmol/L or >22.2 mmol/L.Subjects who are unable or unwilling to cooperate due to hemiplegia after epileptic seizure or other neurological/psychiatric disorders.Known to be allergic to urokinase.Bacterial endocarditis, pericarditis, or acute pancreatitis.Participation in other clinical trials within 30 days before screening.Pregnancy, lactating women, or subjects who do not agree to use effective contraception during the trial.Other conditions deemed by the investigator to impair adherence or pose risks to participants.

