### Procedures

Eligible patients will be screened consecutively and enrolled at Xuanwu Hospital according to the predefined inclusion and exclusion criteria. Upon enrollment, patients will undergo baseline assessments, including electrocardiography, complete blood count, routine serum biochemistry (including liver function, renal function, electrolytes, and blood glucose), and coagulation studies (including prothrombin time, international normalized ratio, activated partial thromboplastin time, fibrinogen, and thrombin time). After informed consent is obtained, a baseline NIHSS examination will be performed (21), and patients will be treated with urokinase at the pre-specified dose calculated for their estimated body weight. In this study, the planned dose levels are 15,000 IU/kg, 20,000 IU/kg, 25,000 IU/kg and 30,000 IU/kg. No patient in any dosage tier will receive more than that dose calculated for a 100 kg person. These dose levels were selected based on the currently recommended empirical dosing range for intravenous urokinase and recent observational dose-exploration data. Dose escalation will proceed according to the following steps.

Firstly, 2 to 6 patients will be enrolled concurrently at the 15,000 IU/kg dose level. (a) If none of the evaluable patients at the current dose level experiences a dose-limiting toxicity (DLT, which is defined below), the dose will be escalated to 20,000 IU/kg. (b) If data for one or more enrolled participants is unavailable, or if one patient develops a DLT at 15,000 IU/kg, the new participant will enter at the same dose level. If one of the first 6 participants experiences a DLT, up to 6 additional participants (for a total of 12) will be enrolled at the same dose level to further assess safety and tolerability. If no more than 2 out of 12 patients experience DLTs, the dose will be escalated to 20,000 IU/kg. If exactly 3 out of 12 patients experience DLTs, the 15,000 IU/kg dose level will be considered the MTD. If more than 3 out of 12 patients develop DLTs, the previous dose (if applicable) will be defined as the MTD, and dose escalation will be halted. (c) If 2 patients experience DLTs at the current dose level before expansion, dose escalation will be terminated, and the previous dose level will be determined as the MTD.

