The exact time of treatment initiation will be documented. Urokinase will be diluted in 100 mL of normal saline and administered via intravenous infusion over 30 min. Upon completion of thrombolysis, patients will be admitted to either the stroke unit or the neuro-intensive care unit and will subsequently receive secondary preventive therapy in accordance with established clinical guidelines (7). Fibrinogen levels will be measured at baseline and at 6 h post-treatment. Non-contrast computed tomography or magnetic resonance imaging will be performed within 36 h after treatment to detect hemorrhage, with additional imaging conducted in cases of clinical deterioration or at the discretion of the treating physicians. All imaging data will be independently reviewed for intracranial hemorrhage by two experienced physicians blinded to patient information. Discrepancies between reviewers will first be resolved by consensus; if disagreement persists, a third senior physician blinded to patient information will adjudicate the case. The final adjudicated result will be used for hemorrhage classification and related safety analyses. Neurological assessments using the NIHSS will be performed at baseline, 24 h, 36 h, and at 7 days or discharge after stroke onset. The Barthel Index (BI) and mRS will be assessed at 7 days or at discharge, and again at 3 months (22, 23). Ischemic stroke subtype will be classified according to the Trial of Org 10,172 in Acute Stroke Treatment criteria at 7 days or discharge, based on all available clinical diagnostic data (24). The mRS score at 90 days will be assessed either in person or via telephone interview. The schedule of enrolment, treatment, and follow-up assessments is summarized in Table 1.

**Table 1 tab1:** Schedule of enrolment, treatment, and outcome assessments in the OUTSET study.

Assessments	Screening/baseline	During urokinase infusion (0–30 min)	6 h post-treatment	24 h	36 h	Day 7 or at discharge	Day 90 (±7 days)
Eligibility assessment (inclusion/exclusion criteria)	×						
Written informed consent	×						
Demographic data	×						
Medical history and vascular risk factors	×						
Previous medication	×						
Physical examination and vital signs	×	×	×	×	×	×	
NIHSS	×			×	×	×	
Pre-stroke mRS	×						
Complete blood count	×						
Serum biochemistry	×						
Coagulation studies	×						
Fibrinogen	×		×				
Brain CT or MRI	×				×		
Urokinase administration		×					
Documentation of treatment start time		×					

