### DLT

We pre-defined the DLT before the start of the study, which included any of the following adverse events during the procedure:

Symptomatic intracranial hemorrhage within 36 h after IVT (25).Parenchymal hemorrhage type 2 within 36 h after IVT (26).Major bleeding and clinically relevant non-major bleeding within 36 h after IVT (27, 28).

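### One INR/PT limit covers all oral anticoagulants, so recent direct oral anticoagulant intake with both tests within limits meets no explicit anticoagulant exclusion

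*Protocol article*

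**What the plan says.** The relevant exclusion criteria are in the Participants section of the protocol article.

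- Oral anticoagulants: "On oral anticoagulants (e.g., warfarin) with INR >1.7 or PT >15 s".
- Heparin: "Having received heparin treatment within 24 h". This is a time window and applies whatever the laboratory result.
- Bleeding tendency in general: "Propensity for acute bleeding, including platelet count <100 × 10^9^/L or otherwise".
- Final catch-all: "Other conditions deemed by the investigator to impair adherence or pose risks to participants".

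Under Procedures, the baseline coagulation panel includes PT, INR, aPTT, fibrinogen and thrombin time. Table 1 lists "Previous medication" at screening/baseline.

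The DLT section defines a DLT as "any of the following adverse events during the procedure" and then lists three kinds of event: symptomatic intracranial haemorrhage, parenchymal haemorrhage type 2, and "Major bleeding and clinically relevant non-major bleeding within 36 h after IVT". The first two carry the same 36 h window.

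**The concern.** INR and PT are a natural way to judge the effect of warfarin. The criterion extends them to every oral anticoagulant. As general pharmacology, which the document does not state, both tests can be close to normal shortly after a dose of a direct thrombin or factor Xa inhibitor. If so, the limit does not screen for what it is meant to screen for in that class.

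Two things are at stake. The first is patient safety: someone with an active anticoagulant on board could receive a thrombolytic at a dose that rises by cohort to 30,000 IU/kg. The second is attribution: the MTD rests on a handful of bleeding events, and a bleed due partly to co-medication would be counted as toxicity of the urokinase dose.

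**Working it through.** The plan gives no figure to reproduce. The check is a reading of the eligibility list against one defined patient, followed by the consequence under the DLT and escalation rules.

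**Test patient.** Direct oral anticoagulant taken recently; INR at or below 1.7; PT at or below 15 s; no heparin in the previous 24 h; platelets at or above 100 × 10^9/L; otherwise eligible.

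**Criteria in turn.**

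1. Oral anticoagulant item: the patient is on an oral anticoagulant, but neither laboratory limit is exceeded. Not excluded.
2. Heparin item: a different drug. Not excluded.
3. aPTT and thrombin time: both are measured at baseline, but neither has an exclusion limit in the list. Not excluded.
4. Bleeding-propensity item: the platelet limit is one instance and the wording is open. The patient may be excluded, depending on how the item is read.
5. Investigator catch-all: the patient may be excluded, at the investigator's discretion.

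No other exclusion names a direct oral anticoagulant, a time since its last dose, or an assay for it. The patient therefore meets no explicit anticoagulant exclusion, and only items 4 and 5 can keep the patient out.

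**Consequence if such a patient is enrolled and bleeds.** All three listed DLTs are bleeds within 36 h, and none requires a judgement that urokinase was the cause. The bleed counts in full. Under Procedures, "If one of the first 6 participants experiences a DLT, up to 6 additional participants (for a total of 12) will be enrolled", and two DLTs before expansion end escalation and set the previous level as the MTD. An extra bleed from co-medication can only push towards expansion, stopping or a lower MTD. It cannot make a dose look safer than it is.

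**Size.** The number of such patients, their excess bleeding risk and how often item 4 or 5 would be used are not in the document, so no effect on the escalation decision can be derived.

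**The case against.** The strongest reply is that the list already deals with this patient. The bleeding-propensity item is not worded as investigator opinion, its platelet limit is only an instance, and recent anticoagulant intake fits its plain meaning. The catch-all is a second route, and the investigator has the medication history, aPTT and thrombin time at hand. This stands in part: exclusion is possible. It does not settle the matter, because a specific criterion with numeric limits can be read as clearing an anticoagulated patient who falls within them, and the decision is taken under time pressure in a 6 h treatment window.

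A second reply is that this is a condensed article, and that the item is really a warfarin rule with other drugs left to the full protocol. But the article prints a long list and gives this item its own limits, and its wording makes warfarin an example. The point concerns a rule that is stated, not a missing detail.

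Three further objections hold and limit the point. The insensitivity of INR and PT comes from outside the document, and without it there is no reason to think the limit fails. The Discussion justifies excluding endovascular therapy by confounding from mechanical reperfusion; that is a useful analogy but does not commit the trial to removing every bleeding confounder. Table 1 does not list time of last dose, so a window is not free of cost.

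A reader might infer that the gap sharply reduces the chance of escalating past a dose level. The document does not support this. One DLT among the first six does make escalation less likely, but that is true of a DLT in any patient. It shows the cost of one event under the rules, not the effect of this wording.

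**Conclusion.** The point holds as a gap in safety and attribution that is likely to arise rarely. One INR/PT limit is fixed for all oral anticoagulants, and a patient with recent direct oral anticoagulant intake and both tests within limits is kept out only by an open-ended item or by discretion. It rests on one stated assumption from outside the document: that these tests can be near normal after such intake.

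The likely effect on escalation is small, since such patients are probably few and the general items may exclude them. Its direction is conservative: an early stop or an MTD set too low. Two stronger readings are not supported. The protocol does not positively admit these patients, and nothing here suggests that an unsafe dose would be declared tolerable. DSMB review of DLTs does not close the gap, because it comes after the patient has been exposed. The priority is optional to moderate, and the case for acting rests mainly on patient safety and the low cost of the change.

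**What to change.** Restrict the INR/PT limit to vitamin K antagonists. Add one fixed exclusion for any direct oral anticoagulant taken within a stated window before treatment. The sponsor should set and justify the window; the document offers 24 h, from the heparin item, as a minimum. No general aPTT or thrombin-time limit is needed. Those baseline results can serve as supporting evidence where direct oral anticoagulant use is known or suspected.

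The cost is one amended criterion and a question at screening about the time of the last dose, which the heparin item already requires for that drug. No new laboratory test is needed. There will be a few more screen failures.

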### Procedures

Eligible patients will be screened consecutively and enrolled at Xuanwu Hospital according to the predefined inclusion and exclusion criteria. Upon enrollment, patients will undergo baseline assessments, including electrocardiography, complete blood count, routine serum biochemistry (including liver function, renal function, electrolytes, and blood glucose), and coagulation studies (including prothrombin time, international normalized ratio, activated partial thromboplastin time, fibrinogen, and thrombin time). After informed consent is obtained, a baseline NIHSS examination will be performed (21), and patients will be treated with urokinase at the pre-specified dose calculated for their estimated body weight. In this study, the planned dose levels are 15,000 IU/kg, 20,000 IU/kg, 25,000 IU/kg and 30,000 IU/kg. No patient in any dosage tier will receive more than that dose calculated for a 100 kg person. These dose levels were selected based on the currently recommended empirical dosing range for intravenous urokinase and recent observational dose-exploration data. Dose escalation will proceed according to the following steps.

Firstly, 2 to 6 patients will be enrolled concurrently at the 15,000 IU/kg dose level. (a) If none of the evaluable patients at the current dose level experiences a dose-limiting toxicity (DLT, which is defined below), the dose will be escalated to 20,000 IU/kg. (b) If data for one or more enrolled participants is unavailable, or if one patient develops a DLT at 15,000 IU/kg, the new participant will enter at the same dose level. If one of the first 6 participants experiences a DLT, up to 6 additional participants (for a total of 12) will be enrolled at the same dose level to further assess safety and tolerability. If no more than 2 out of 12 patients experience DLTs, the dose will be escalated to 20,000 IU/kg. If exactly 3 out of 12 patients experience DLTs, the 15,000 IU/kg dose level will be considered the MTD. If more than 3 out of 12 patients develop DLTs, the previous dose (if applicable) will be defined as the MTD, and dose escalation will be halted. (c) If 2 patients experience DLTs at the current dose level before expansion, dose escalation will be terminated, and the previous dose level will be determined as the MTD.

The exact time of treatment initiation will be documented. Urokinase will be diluted in 100 mL of normal saline and administered via intravenous infusion over 30 min. Upon completion of thrombolysis, patients will be admitted to either the stroke unit or the neuro-intensive care unit and will subsequently receive secondary preventive therapy in accordance with established clinical guidelines (7). Fibrinogen levels will be measured at baseline and at 6 h post-treatment. Non-contrast computed tomography or magnetic resonance imaging will be performed within 36 h after treatment to detect hemorrhage, with additional imaging conducted in cases of clinical deterioration or at the discretion of the treating physicians. All imaging data will be independently reviewed for intracranial hemorrhage by two experienced physicians blinded to patient information. Discrepancies between reviewers will first be resolved by consensus; if disagreement persists, a third senior physician blinded to patient information will adjudicate the case. The final adjudicated result will be used for hemorrhage classification and related safety analyses. Neurological assessments using the NIHSS will be performed at baseline, 24 h, 36 h, and at 7 days or discharge after stroke onset. The Barthel Index (BI) and mRS will be assessed at 7 days or at discharge, and again at 3 months (22, 23). Ischemic stroke subtype will be classified according to the Trial of Org 10,172 in Acute Stroke Treatment criteria at 7 days or discharge, based on all available clinical diagnostic data (24). The mRS score at 90 days will be assessed either in person or via telephone interview. The schedule of enrolment, treatment, and follow-up assessments is summarized in Table 1.

**Table 1 tab1:** Schedule of enrolment, treatment, and outcome assessments in the OUTSET study.

Assessments	Screening/baseline	During urokinase infusion (0–30 min)	6 h post-treatment	24 h	36 h	Day 7 or at discharge	Day 90 (±7 days)
Eligibility assessment (inclusion/exclusion criteria)	×						
Written informed consent	×						
Demographic data	×						
Medical history and vascular risk factors	×						
Previous medication	×						
Physical examination and vital signs	×	×	×	×	×	×	
NIHSS	×			×	×	×	
Pre-stroke mRS	×						
Complete blood count	×						
Serum biochemistry	×						
Coagulation studies	×						
Fibrinogen	×		×				
Brain CT or MRI	×				×		
Urokinase administration		×					
Documentation of treatment start time		×					
DLT assessment		×	×	×	×		
Intracranial hemorrhage assessment					×		
Barthel index						×	×
Modified rankin scale						×	×
TOAST classification						×	
Adverse events and serious adverse events		×	×	×	×	×	×
All-cause mortality							×

NIHSS, National Institutes of Health Stroke Scale; mRS, modified Rankin Scale; DLT, dose-limiting toxicity; TOAST, Trial of Org 10,172 in Acute Stroke Treatment; CT, computed tomography; MRI, magnetic resonance imaging. Brain CT or MRI will be performed within 36 h after treatment to assess intracranial hemorrhage. Additional imaging may be performed in the event of clinical deterioration or when clinically indicated. Day 90 follow-up may be conducted during an outpatient visit or by telephone interview.

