### Sample size

The sample size was determined by the rolling-six dose-escalation design rather than by a conventional efficacy-based power calculation. Under this design, 2 to 6 participants may be enrolled concurrently at each dose level, and dose-escalation decisions are based on the number of participants currently enrolled and evaluable, the number who experience DLTs, and the number who remain under DLT observation (16). Therefore, 6 participants represent the maximum initial evaluable cohort size for dose-escalation decisions at a given dose level, rather than the total number considered sufficient for the entire study (16, 20). Published applications of the rolling-six framework have shown that the total number enrolled at a given dose level may exceed 6 because non-evaluable participants can be replaced and additional patients may be enrolled to further characterize safety after a dose level has been judged acceptable (19, 20). In our protocol, participants who are not evaluable for dose-escalation decisions will be replaced according to the prespecified rolling-six rules, and if one DLT occurs among the first 6 evaluable participants at a dose level, that cohort may be expanded to 12 participants for further safety evaluation. With four planned dose levels, the expected total sample size ranges from 24 to 48 participants, depending on the occurrence of DLTs and cohort expansion.

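### The sample size range of 24 to 48 does not follow from the escalation rule, whose text sets no minimum evaluable count and no refill of a level named the MTD by stepping back

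*Protocol article*

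**What the plan says.** Procedures opens the escalation with "Firstly, 2 to 6 patients will be enrolled concurrently at the 15,000 IU/kg dose level". The branches that matter here are:

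- **(a)** The escalation condition is "If none of the evaluable patients at the current dose level experiences a dose-limiting toxicity". No evaluable count is attached to it.
- **(b)** The next patient stays at the same level if data are unavailable for an enrolled patient or if one DLT has occurred. One DLT in the first six leads to expansion to 12. Up to 2 of 12 escalates. At three, "If exactly 3 out of 12 patients experience DLTs, the 15,000 IU/kg dose level will be considered the MTD". Beyond that, "If more than 3 out of 12 patients develop DLTs, the previous dose (if applicable) will be defined as the MTD".
- **(c)** With two DLTs before expansion, escalation ends and "the previous dose level will be determined as the MTD".

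The Sample size section says that "6 participants represent the maximum initial evaluable cohort size for dose-escalation decisions at a given dose level". It then says that, over four levels, "the expected total sample size ranges from 24 to 48 participants", "depending on the occurrence of DLTs and cohort expansion".

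The Figure 1 caption says the figure bases decisions on the numbers enrolled and evaluable, the DLTs, and the patients still at risk. The figure itself is not shown.

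**The concern.** Two things do not fit together.

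First, the lower end of the sample size range treats six patients per level as a floor, while the same paragraph describes six as a ceiling for the initial cohort and Procedures allows as few as two. The range also takes no account of a trial that stops before the fourth level.

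Second, two enrolled, evaluable, DLT-free patients satisfy branch (a) and do not trigger branch (b). If the next level then fails, the level below becomes the MTD as it stands. The text has no step that brings it to six first.

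The MTD is the primary endpoint and is meant to inform phase II/III trials. On the prose alone, it could rest on two patients.

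**Working it through.** **Inputs from the article.** Four dose levels; two to six patients enrolled concurrently per level; expansion to 12 after one DLT in the first six; the DLT thresholds quoted above. The article gives no target or expected DLT rate, so every rate *p* below is an assumption.

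**1. Reproducing the stated range.** 4 × 6 = 24 and 4 × 12 = 48. Both ends reproduce. The 24 needs all four levels to be reached with at least six patients at each.

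**2. The lower bound under the written rule.** If *k* evaluable patients without a DLT suffice, four clean levels need 4*k* patients:

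| *k* required | Four DLT-free levels |
|---|---|
| 2 | 4 × 2 = 8 |
| 3 | 4 × 3 = 12 |
| 6 | 4 × 6 = 24 |

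Early stopping goes lower. With six per level, two DLTs at level 1 before expansion end the trial with at most 6 patients. A clean level 1 followed by two DLTs at level 2 before expansion ends it with at most 6 + 6 = 12.

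**3. How often the total falls below 24.** Exact enumeration over four levels at a flat *p* = 0.10, with the first look at *k* patients:

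| *k* | Mean total | P(total < 24) |
|---|---|---|
| 2 | 11.7 | 94% |
| 3 | 15.9 | 88% |
| 6 | 25.7 | 31% |

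At a flat *p* = 0.05, P(total < 24) is 97%, 93% and 10%. Small differences (for example 87% instead of 88% for *k* = 3 at 10%) arise from whether patients already enrolled when the second DLT occurs are counted.

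**4. Chance of clearing a level.** With the first look at *k*, filling to six after one DLT and expanding after 1 of 6:

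P(pass) = (1−p)^k + k·p·(1−p)^5·P(Bin(6,p) ≤ 1)

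For example, at *p* = 0.25 and *k* = 2: 0.5625 + 2 × 0.25 × 0.2373 × 0.5339 = 0.626.

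| *p* | *k* = 2 | *k* = 3 | *k* = 6 |
|---|---|---|---|
| 0.10 | 0.915 | 0.886 | 0.845 |
| 0.25 | 0.626 | 0.517 | 0.368 |
| 0.40 | 0.375 | 0.238 | 0.090 |

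The exact two-sided 95% upper limit for the DLT rate after 0 of *n* is 1 − 0.025^(1/n): 84% for 0/2, 71% for 0/3 and 46% for 0/6.

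**5. Effect of filling a 0/2 level to six before naming it the MTD.** Four patients are added. Two or more DLTs among them fail the level. Exactly one leads to expansion by six, and three or more further DLTs (at least 4 of 12) fail it:

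P(step down) = P(Bin(4,p) ≥ 2) + P(Bin(4,p) = 1)·P(Bin(6,p) ≥ 3)

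| *p* | Numbers | Step down |
|---|---|---|
| 0.10 | 0.0523 + 0.2916 × 0.0159 | 6% |
| 0.25 | 0.2617 + 0.4219 × 0.1694 | 33% |
| 0.30 | 0.3483 + 0.4116 × 0.2557 | 45% |
| 0.40 | 0.5248 + 0.3456 × 0.4557 | 68% |

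**The case against.** The strongest reply is that Figure 1 carries the decision rule. Its caption refers to evaluable patients, so a minimum count may well stand there, and a figure lost in reading is not missing from the plan. The phrase about two to six patients concerns concurrent enrolment, and much of the rest counts in sixes. This stands to the extent that one cannot conclude the trial will escalate on two patients. A reader might infer that from Procedures, but the documents at hand do not settle it. Whatever Figure 1 says, the sample size range still needs correcting: a minimum below six makes 24 too high for four clean levels, and a minimum of six still leaves 24 broken by early stopping.

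Three further points also limit the concern:

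- A reader might take the Sample size section to say that the total depends on DLTs and expansion alone. It does not say so. It lists them, mentions replacement of non-evaluable patients just before, and calls the range expected.
- A reader might take all the step-down probabilities as unsafe doses caught. They are not. A 25% DLT rate is one that the 3-of-12 rule itself accepts as the MTD, so the 33% there, like the 6% at a 10% rate, includes stepping down from an acceptable dose.
- The DSMB reviews all DLTs and can recommend changes. That lowers the risk, although the article gives the board no minimum count either.

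**Conclusion.** The point holds for the lower end of the sample size range and, conditionally on Figure 1, for the escalation text. The 24 is not a lower bound under the rule as written. It is the total for four clean levels only if six are required at each, and 12 or 8 if three or two are. Even at six per level, 31% of trials would end below 24 at an assumed flat 10% DLT rate. The upper end of 48 is correct as a ceiling on evaluable patients.

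On the visible text, a level cleared at 0/2 can become the MTD with no further patients. The figures for *k* = 2 show what that reading allows; they do not predict what the trial will do. Filling such a level to six would move the MTD down in 45% of cases at an assumed 30% rate and 68% at 40%, at the price of some needless steps down at lower rates.

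**What to change.** 1. State in rule (a) how many evaluable patients with a completed 36 h window are needed to escalate at 0 DLTs, using the same number as Figure 1. This is a wording change.
2. Restate the sample size as the evaluable patients needed to complete all four levels: lower bound 24, 12 or 8 if six, three or two are required, and ceiling 48. Add that early stopping gives fewer and that replaced patients come on top. This is also a wording change.
3. Require six evaluable patients at a level before it is named the MTD. If it has fewer, fill it and apply the existing DLT rules. If it then fails, treat the next level down in the same way.

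Item 3 costs four patients for a level at 0/2, and up to ten (4 + 6) if one of those four has a DLT and the level expands. The same cost recurs for each lower level if the filled level fails: up to about 30 (3 × 10) over three levels. No level exceeds 12, so the trial stays within the planned 48 evaluable patients. The other cost is the occasional step down from an acceptable dose: about 6% at an assumed 10% DLT rate and 33% at 25%. Escalation can keep its flexible speed, because six are needed only at the level that is named.
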